## Discussion

Angiogenesis plays a pivotal role in the growth of the endometrium and embryo implantation [19,20]. During the transition of the endometrium from the proliferative to the secretory phase, there is a gradual increase in endometrial blood flow, and abundant endometrial blood supply is crucial for successful embryo implantation [21]. Dynamic transvaginal ultrasound monitoring of changes in uterine arteries, endometrium, and sub-endometrial angiogenesis can effectively assess endometrial blood supply. A meta-analysis [22] revealed statistically significant differences in endometrial VI, FI, VFI on the day of embryo transfer, and sub-endometrial vascular FI on the day of human chorionic gonadotropin (hCG) injection between pregnant and non-pregnant women following assisted reproductive technology treatment, suggesting a potential relationship between these blood flow parameters and pregnancy occurrence. However, some studies have questioned the relationship between endometrial blood flow indices under ultrasound and endometrial receptivity. For instance, Mayer et al. [23] found no statistically significant differences in endometrial and sub-endometrial VI, VFI, and FI on the day of transfer between pregnant and non-pregnant women in frozen embryo transfer cycles. Similarly, Zhang et al. [24] reported no statistically significant differences in uterine PI, RI, and endometrial and sub-endometrial VI, FI, VFI on the day of hCG injection between pregnant and non-pregnant groups, as well as between miscarriage and ongoing pregnancy groups, suggesting that blood flow-related parameters of the endometrium and sub-endometrium cannot accurately assess endometrial receptivity.

However, most prior studies have relied on retrospective analysis, potentially yielding biased results. Hence, prospective research remains essential to evaluate the feasibility and precision of ultrasound-derived uterine blood flow parameters in predicting the optimal embryo transfer timing in IVF. This protocol outlines a prospective, cross-sectional study that explores the role of ultrasound in pre-embryo transfer diagnostics. Building on this, we have pioneered the use of MV-FLOW^™^ to detect microvascular distribution within the endometrium and sub-endometrium, and validated its feasibility in assessing endometrial vasculature [11]. SVC [25] is a common supervised machine learning algorithm that seeks an optimal hyperplane in feature space to discriminate between different classes, characterized by excellent generalization capabilities. We propose to input all ultrasound-derived uterine blood flow parameters as flow features to predict embryo implantation outcomes and rates, thereby identifying the most predictive ultrasound indices for embryo implantation and discussing the diagnostic value of MV-FLOW^™^ in assessing endometrial receptivity. RIF is predominantly influenced by embryonic or uterine factors, with studies indicating abnormal blood flow parameters [26]. Our study extends this by investigating the clinical utility of these parameters in differentiating between successful first-time transfers and RIF cases, offering predictive markers for RIF identification.

In conclusion, while we have discussed the potential effects of MV-FLOW^™^ in predicting frozen embryo transfer outcomes in patients with recurrent implantation failure, it is important to consider the broader clinical implications should our study’s predictions prove accurate. Successful prediction models could revolutionize personalized treatment plans, allowing clinicians to tailor interventions more effectively and improve overall success rates in assisted reproductive technologies. This could lead to a paradigm shift in how recurrent implantation failure is managed, ultimately enhancing patient outcomes and satisfaction. Furthermore, the integration of MV-FLOW^™^ with multidimensional ultrasound features could pave the way for more comprehensive diagnostic tools, offering deeper insights into the underlying causes of implantation failure and facilitating more targeted therapeutic strategies.

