This study, grounded in a current cross-sectional investigation employing support vector classification (SVC) algorithms, aims to explore: (1) the predictive precision of MV-FLOW^™^ endometrial vascular distribution indices and/or endometrial vascular indices for FET outcomes in RIF patients; (2) the potential of these indices to categorize patients as either successful first implantation (FI) or RIF.

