## Methods and materials

### Study design

We will recruit a cross-sectional observational cohort of FI and RIF patients from Jinxin Sinan Women’s and Children’s Hospital in Sichuan who underwent FET. These patients will undergo transvaginal ultrasound examination, including assessment of endometrial MV-FLOW^™^ prior to embryo transfer in FET. First, the foundational clinical data of RIF patients, along with endometrial ultrasound-related indices, will serve as features to forecast the clinical outcome of FET. Subsequently, a clinical prediction model grounded in multidimensional ultrasound features will be developed. The efficacy of this model will be rigorously assessed and subjected to cross validation. Then, the characteristics observed under transvaginal ultrasound examination in successful FI and RIF patients will be employed as predictive indicators to ascertain whether they can effectively categorize successful FI and RIF patients post-transplantation. The dates of the recruitment are July 15^th^, 2024 to July 15^th^, 2025. We will also establish a flexible recruitment timeline, allowing for adjustments as needed, and regularly monitor and evaluate the recruitment progress, enabling us to identify and address any issues promptly. All obtained private data will be subject to the supervision of the ethics committee, and the study will be conducted after patients have signed the informed consent form. This trial was reviewed by the ethics committee of Sichuan Jinxin Xi’nan Women’s and Children’s Hospital (2023–006), and registered in Chinese Clinical Trial Registry (ChiCTR2400086401) (See S1 Table). Study flow chart see Figs 1 and 2 and S2 Table (the SPIRIT schedule of enrollment).

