**Fig 2 pone.0316028.g002:**
[figure not shown]
The schedule of enrolment, interventions, and assessments. Note: *-t1: Eligibility screen and informed consent before frozen embryo transfer; 0: Allocation at the beginning of frozen embryo; t1: Ultrasound analysis at the day before embryo transfer; t2: Biochemical pregnancy at 14 days following embryo transfer; t3: Clinical pregnancy and embryo implantation at 28 days after embryo transfer.

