### Participants and sample size

#### Diagnostic criteria for RIF patients

According to the definition of RIF proposed by EHSRE 2023 [12], the transfer of embryos considered viable fails to result in a positive pregnancy test for a given patient and is insufficient to consider further investigation and/or intervention. Considering that the recommended threshold for the cumulative predicted chance of implantation for RIF is 60%, when a couple does not successfully implant by transferring a certain number of embryos and the cumulative predicted chance of implantation associated with that number is greater than 60%, then they should be advised to undergo further investigations and/or treatment options.

For embryos of unknown euploidy [13], RIF is diagnosed in female patients under 35 years old after three or more embryo transfers (ET); for those aged 35 to 39, after four or more ETs; and for those aged 40 and above, after six or more ETs. For embryos with known ploidy status [14], RIF is diagnosed after two or more ETs.

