#### Diagnostic criteria for FI patients

FI patients are defined as patients who have not previously undergone fresh or frozen embryo transfer.

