#### Sample size calculation

This study is a cross-sectional trial to establish a predictive model for endometrial receptivity and pregnancy outcomes using SVC to predict clinical pregnancy. The ultrasound assessments of uterine arteries and endometrial thickness are crucial for pre-implantation evaluation of endometrial receptivity, a study involving 78 FET patients (resulting in 45 clinical pregnancies, 57.7%) utilized elastic ultrasound imaging and nine predictive indicators based on basic information, achieving a predictive accuracy of 76.92% [15]. Sample size estimation was conducted using “pmsampsize” in R software [16]. According to the definition of RIF, at least two failed ETs were diagnosed as RIF. Assuming a clinical pregnancy rate of 30%, a minimum of 323 RIF patients were required for sample estimation. In a 1:1 ratio, 323 FI patients were also included. The code for sample size calculation is referenced in S1 Fig.

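### Aim 2 separates groups already fixed by transfer history and selects only one of them on the current outcome, so it cannot yield predictive markers for RIF

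*Protocol article*

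**What the plan says.** **How the groups are defined.** RIF is a count of past transfers that depends on age and embryo ploidy. Under Diagnostic criteria for RIF patients, "RIF is diagnosed in female patients under 35 years old after three or more embryo transfers (ET"), with four or more at 35 to 39, six or more from 40, and two or more when ploidy is known. On the other side, "FI patients are defined as patients who have not previously undergone fresh or frozen embryo transfer". Having one of these two diagnoses is an inclusion criterion.

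**Order of events.** The note to Fig 2 puts "Eligibility screen and informed consent before frozen embryo transfer" at -t1, the ultrasound at t1 on the day before transfer, and outcomes at 14 and 28 days after transfer. Nothing is scheduled after day 28.

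**Aim 2.** The Introduction asks about "the potential of these indices to categorize patients as either successful first implantation (FI) or RIF". Study design uses the ultrasound characteristics to "ascertain whether they can effectively categorize successful FI and RIF patients post-transplantation". The Discussion presents the contrast of first transfers that succeeded with RIF as "offering predictive markers for RIF identification".

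**The pregnancy model and numbers.** The Introduction (aim 1) and Study design build the outcome model from RIF patients. The Abstract names both groups of 323 and then gives clinical pregnancy as the label for training. Under Sample size calculation, the RIF number rests on a 30% clinical pregnancy rate, and then "In a 1:1 ratio, 323 FI patients were also included".

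**The concern.** A patient must already be classed as RIF or FI to be enrolled. A scan done afterwards cannot predict that class, and it is not needed to identify it, because the record already does. A difference in blood flow between the groups may have preceded the failed transfers, or it may have followed from those cycles and their treatment. This design cannot separate the two. A reader who takes the Discussion at its word would believe that the study had found markers of who will go on to develop RIF.

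The second problem lies in the label. One class is conditioned on the outcome of the current transfer and the other is not. Any marker of pregnancy in the current cycle will therefore tend to separate the classes, whether or not it has anything to do with RIF. A positive aim 2 result could arise from that alone and be reported as a finding about RIF.

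**Working it through.** **1. The protocol's own figure.** Sample size calculation gives 323 RIF patients at a 30% pregnancy rate. Estimating overall risk to within ±0.05 needs n = (1.96/0.05)² × p(1 − p) = 1536.64 × 0.30 × 0.70 = 322.69, which rounds up to 323. The criterion and margin are assumed, since the code is in a figure that is not shown, but the match is exact. The figure concerns clinical pregnancy in RIF patients. The FI number is copied from it by the 1:1 ratio, so no stated calculation addresses aim 2.

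**2. Can any patient become RIF under observation?** The lowest threshold in the RIF definition is two transfers. An FI patient enters with none and is followed through one. Nobody can cross the threshold before follow-up ends, so the study contains no incident RIF to predict.

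**3. Who is in the aim 2 classes?** No FI pregnancy rate is given. As an assumed range, take 30% (the planning rate for RIF) to 57.7% (the 78-patient study cited for the sample size).

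| Assumed FI rate | Successful FI | FI in neither class | RIF : successful FI |
|---|---|---|---|
| 30% | 323 × 0.30 ≈ 97 | 226 | 3.33 : 1 |
| 57.7% | 323 × 0.577 ≈ 186 | 137 | 1.74 : 1 |

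The contrast is no longer 1:1, and 137 to 226 scanned and followed FI patients fall in neither class.

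**4. Effect of the mixed label.** Take a marker that depends only on current-cycle pregnancy, with AUC A for pregnant versus not pregnant, and has no relation to RIF history. Every successful FI patient is pregnant. Of RIF patients, 30% are pregnant and 70% are not. A random successful FI patient is then compared with a pregnant RIF patient 30% of the time (chance, 0.5) and with a non-pregnant one 70% of the time (A):

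Aim 2 AUC = 0.3 × 0.5 + 0.7 × A

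- A = 0.60: 0.15 + 0.42 = 0.57
- A = 0.70: 0.15 + 0.49 = 0.64
- A = 0.80: 0.15 + 0.56 = 0.71

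**5. The same marker with all FI patients retained.** If a proportion f of FI patients conceive, the same reasoning gives AUC = 0.5 + (f − 0.30)(A − 0.5). Setting f = 1 returns the results in step 4. At f = 0.30 the AUC is 0.50 for any A. At f = 0.577 it is 0.5 + 0.277 × 0.10 = 0.528, 0.5 + 0.277 × 0.20 = 0.555 and 0.5 + 0.277 × 0.30 = 0.583 for A = 0.60, 0.70 and 0.80. What remains reflects a real difference in pregnancy rate between the groups, not the selection of one of them.

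**The case against.** The best defence is that aim 2 does not claim to forecast RIF. The Introduction and Study design speak of categorizing, the Discussion sentence begins with differentiating, and the study is called cross-sectional throughout. Calling the ultrasound features predictive indicators may mean no more than classifier inputs. On that view the fault is one closing clause. This stands in part: the overstatement is concentrated in the Discussion, and much of the repair is wording. It does not answer the label problem, which sits in the aim itself. Study design alone might be read as applying success to both groups, but the Introduction and Discussion attach it to first transfers only.

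A reader might go further and infer that FI outcomes are left unused, or that the pregnancy model is never tested in FI patients. The document does not support that. Outcomes are to be obtained without restriction to one group, FI outcomes define the successful class, and the Abstract can be read as training on both groups. What is established is narrower: the Abstract does not agree with the RIF-only model in the Introduction and Study design. Nor is the absence of a test in FI patients an error against the stated aims, since aim 1 is deliberately about RIF patients.

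A reader might also gauge the problem by how precisely an AUC could be estimated in FI patients compared with a RIF hold-out set. Those are different quantities in different populations, and neither measures this defect.

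**Conclusion.** The point holds in this form. The design cannot support a claim of predictive markers for RIF, because status is fixed and known before the scan and no patient is followed beyond one transfer. This rests on definitions, timing and a stated conclusion that are all fixed in the article, so an unseen analysis plan could not change it. Aim 2 can still describe an association with existing RIF; it would be too strong to call it worthless.

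The label problem is a matter of size. With 30% of RIF patients conceiving, a pure pregnancy marker of AUC 0.60 to 0.80 gives an aim 2 AUC of about 0.57 to 0.71. This assumes that the marker behaves alike in both groups given the outcome. A lower RIF pregnancy rate would enlarge the effect and a higher one would shrink it. The counts of FI patients set aside (137 to 226) depend on an assumed FI rate.

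The change is worth making: it costs little and alters what the study may conclude.

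**What to change.** 1. State aim 2 and the matching Discussion claim as an association of ultrasound features with existing RIF history. Delete the clause about predictive markers for identifying RIF. Compare RIF with all 323 FI patients, not only the successful ones. Rewording alone is not enough, because successful FI versus RIF would still mix history with current outcome.

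2. Reconcile the Abstract with the Introduction and Study design on who trains the pregnancy model. If it is trained on RIF patients only, also apply it unchanged to all FI patients, using only predictors defined in both groups (prior-transfer history is not), and report AUC and calibration there separately as a test of transport. If both groups train the model, the FI patients are not independent of it and this test does not apply; the Introduction and Study design should then say that both groups are used.

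The cost is a more modest claim, probably a lower aim 2 AUC, and a little extra analysis of data already being collected. No new patients or measurements are needed.
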